## **7.3 Adverse Events and Serious Adverse Events**

An adverse event (AE) is any untoward medical occurrence in a subject during participation in the clinical study or with use of the experimental agent being studied. An adverse finding can include a sign, symptom, abnormal assessment (laboratory test value, vital signs, electrocardiogram finding, etc.), or any combination of these.

A serious adverse event (SAE) is any AE that results in one or more of the following outcomes:

- Death
- A life-threatening event
- Inpatient hospitalization or prolongation of existing hospitalization
- A persistent or significant disability/incapacity
- A congenital anomaly or birth defect
- An important medical event based upon appropriate medical judgment

We will utilize the NCI Common Terminology Criteria for adverse Events which are a descriptive terminology that can be utilized for Adverse Event (AE) reporting and provides a grading (severity) scale for each AE. AEs will be labeled according to severity, which is based on their impact on the patient utilizing the following criteria:

Grade refers to the severity of the AE. The CTCAE displays Grades 1 through 5 with unique clinical descriptions of severity for each AE based on this general guideline:

- Grade 1 Mild; asymptomatic or mild symptoms; clinical or diagnostic observations only; intervention not indicated.
- Grade 2 Moderate; minimal, local or noninvasive intervention indicated; limiting age-appropriate instrumental ADL\*.
- Grade 3 Severe or medically significant but not immediately life-threatening; hospitalization or prolongation of hospitalization indicated; disabling; limiting self care ADL\*\*.
- Grade 4 Life-threatening consequences; urgent intervention indicated.
- Grade 5 Death related to AE.

A Semi-colon indicates 'or' within the description of the grade.

A single dash (-) indicates a grade is not available.

#### **A. AE Attribution Scale**

Attribution: An assessment of the relationship between the AE and the medical intervention will be performed using the following the NCI guidelines which do not define an AE as necessarily “caused by a therapeutic intervention”, after naming and grading the event, the clinical investigator will assign an attribution to the AE using the following attribution categories:

| RELATIONSHIP                                                 | ATTRIBUTION | DESCRIPTION                                              |
|--------------------------------------------------------------|-------------|----------------------------------------------------------|
| Unrelated to investigational agent/intervention  | Unrelated   | The AE is clearly NOT related to the intervention |
|                                                              | Unlikely    | The AE is doubtfully related to the intervention  |
| Related to investigational agent/intervention    | Possible    | The AE may be related to the intervention         |
|                                                              | Probable    | The AE is likely related to the intervention      |
|                                                              | Definite    | The AE is clearly related to the intervention     |

#### 7.4 Reporting Procedures

SAEs that are unanticipated, serious (Grade 3), and possibly related to the study intervention will be reported to the Independent Monitor(s), IRB, and NCCIH in accordance with requirements.

- Unexpected fatal or life-threatening AEs related to the intervention will be reported to the NCCIH Program Officer and Independent Monitoring Committee within 2 days and to the IRB within 1 day. Other serious and unexpected AEs related to the intervention will be reported to the NCCIH Program Official within 7 days.
- Other anticipated or unrelated SAEs will be handled in a less urgent manner but will be reported to the Independent Monitor(s), IRB, NCCIH, and other oversight organizations in accordance with their requirements. In the annual AE summary, the Independent Monitor(s) Report will state that they have reviewed all AE reports.

#### 7.5 Follow-up for Adverse Events

In instances where an adverse event does occur, we will follow-up with participants until the event is resolved or until the IRB deems it unnecessary to continue to follow the participant.

#### 7.6 Safety Monitoring

There is a completed DSMP for THE RELIEF Study that has been established and submitted to NCCIH.

## 8. INTERVENTION DISCONTINUATION

A subject would be discontinued from the study intervention if a medical condition develops that precludes the continuation of the treatment intervention. For participants who discontinue the RELIEF Study prior to completing all scheduled treatment sessions (regardless of the reason), we will make every attempt to obtain the above-mentioned outcome measurements. If the study participant is unwilling or unable to undergo the laboratory-based tests (e.g., difficulty tolerating the protocol, experienced an adverse event to a lab test) we will still attempt to obtain the clinical outcome measures. In instances where an adverse event does occur, we will follow-up with participants until the event is resolved or until the IRB deems it unnecessary to continue to follow the participant.

## 9. STATISTICAL CONSIDERATIONS

This study (R01 AT006978-01) was primarily designed to investigate the mechanisms underlying the biology of manual therapies. As such, our statistical power considerations are primarily based on the Mechanistic Component of The RELIEF Study. Below we detail the statistical considerations for the Mechanistic Component first, followed by a discussion of statistical considerations for the exploratory Phase II RCT Component. Importantly, this exploratory Phase II RCT with a nested mechanistic design allows us to maximize the data to be generated to address critical clinical and mechanistic questions necessary to improve our understanding of manual therapy treatments from chronic low back pain.

### 9.1 General Design Issues

#### Mechanistic Component

Below we list our primary and secondary hypotheses for the Mechanistic Component. Note that all sample size calculations are based on the primary hypotheses. For more specific information, see *Data Analysis* below.

- Group 1 (Muscular Effects):
  - Primary Hypothesis
    - We hypothesize that there is a significant effect of treatment on skeletal muscle proton transverse relaxation time (T2) asymmetry of the lumbar muscles either immediately following the first treatment intervention (OA2), post-treatment measure (OA3), and/or follow-up measure (OA4), after controlling for the baseline outcome value.
- Group 2 (Spinal Effects)
  - Primary Hypothesis
    - For short-latency stretch reflex excitability, we hypothesize that there is a significant effect of treatment on this outcome at OA2, OA3, and/or OA4, after controlling for the baseline outcome value.
  - Secondary Hypotheses
    - For trunk muscle onset latencies in response to postural perturbations, we hypothesize that there is a significant effect of treatment on the principal component score (i.e., the linear combination of onset latencies of eight muscles) at OA2, OA3, and/or OA4, after controlling for the baseline outcome value.
    - For lumbar motion during volitional movement tasks, we hypothesize that there is a significant effect of treatment on the principal component score at OA2, OA3, and/or OA4, after controlling for the baseline outcome value.
  - See appendix for hypotheses of the supplemental research
- Group 3 (Cortical Effects)
  - Primary Hypothesis
    - We hypothesize that there is a significant effect of treatment on measures indicative of increased intracortical excitability (i.e., increased motor evoked potential amplitude, increased intracortical facilitation, and/or decreased short-interval intracortical inhibition) at either OA2, OA3, and/or OA4, after controlling for the baseline outcome values.

#### RCT Component

To test the following RCT hypotheses, we will collapse the clinical outcome data across the three physiological outcome groups. Our Co-Primary Outcomes are NPR and RMDQ scores. The NPR and RMDQ are classic measures for the assessment of pain and disability in low back pain. Our secondary outcomes are change in PROMIS measures of Pain Behavior, Pain Interference, Pain Intensity, and Physical Function. Our primary endpoint is OA3 (visit 8, 3-days +/-1-day after completion of course of treatment intervention).

- Primary Hypotheses
  - We hypothesize that the Manipulation and the Mobilization groups will display a significantly lower NPR level than the Sham Control at the post-treatment measure (OA3, our primary endpoint) after controlling for the baseline value. Because we have a directional hypothesis, we will use a one-tailed test.
  - We hypothesize that the Manipulation and the Mobilization groups will display a significantly lower RMDQ level than the Sham Control at OA3 after controlling for the baseline value. Because we have a directional hypothesis, we will use a one-tailed test.
- Secondary Hypotheses
  - We hypothesize that the Manipulation and the Mobilization groups will display significantly lower levels in PROMIS Pain Behavior, Interference, Intensity, and/or Physical Function than the Sham Control at OA3 after controlling for the baseline value.

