## 9.2 Sample Size and Randomization

### **Sample Size Calculation for Mechanistic Component**

For each primary hypothesis, sample size to achieve the power of 0.80 was computed using Monte Carlo simulation studies. For all simulation studies, the following were assumed:

- The Type I error rate (the alpha level) was set at 0.05 and the Type II error rate (the beta level = 1 - power) at 0.20.
- A first-order autoregressive temporal structure was assumed with  $\rho$  of -0.50.
- Holm's method was used to adjust the alpha level.
- To produce a plausible attrition rate, 10% of the computer-generated participants dropped out at either 2-days or 4-week post treatment measure completely at random; these participants contributed no scores at subsequent measures. To make the sample-size calculation slightly conservative, missing observations remained missing.
- Linear mixed effects regression (LMER) was used to analyze the data.
- To ensure the acceptable precision, each simulation study was repeated 10,000 times.
- The baseline measure was included as a covariate to improve power and precision of the test.

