### **Sample Size for RCT Component**

Our co-primary outcomes are NPR and RMDQ at the primary endpoint (i.e., 3-days +/-1-day following a course of treatment). As stated previously, we will collapse the clinical outcome data across the three physiological outcome groups for a total sample size of 54/treatment arm. A recent review of a large number of RCTs on the effects of spinal manipulation for the treatment of chronic low back pain indicate that small treatment effect sizes are observed.[62] However, the effect sizes reported for studies that used a clinical prediction rule to identify individuals most likely to respond to manipulation treatment report large effect sizes. (e.g., effect size  $d > 1.3$  for clinically meaningful reductions in disability).[63] The RELIEF Study will use a modified-clinical prediction rule to define a target population of patients with chronic low back pain who are most likely to respond to manual therapy treatment. However, because our population is chronic

rather than acute (a factor in the original clinical prediction rule) we took a more conservative approach and based our power calculations on the assumption of a moderate treatment effect (i.e., effect size  $d=0.5$ ) to reduce disability.

- Our calculations are based on an assumed moderate effect size (effect size  $d=0.5$ ; based on data from Maughan and Lewis' work indicating standard deviations for NPR being 2.5 and RMDQ being 6 for patients with chronic low back pain).[64] Our simulation studies indicate that 54 subjects/treatment arm is sufficient to achieve power of 0.80 to detect a significant treatment effect at our primary endpoint (i.e., 2-days following the course of treatment) given an attrition rate of 10% and appropriate alpha adjustments. With this sample size we have sufficient power to detect changes in  $NPR > 2$  and  $RMDQ > 3$ , which are the classically defined levels of clinically-meaningful important differences in these outcomes.

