### **RCT Component**

To test the following RCT hypotheses, we will collapse the clinical outcome data across the three physiological outcome groups for a total sample size of 54/treatment arm.

- Primary Hypotheses
  - We will use separate analyses to test whether the manipulation or mobilization treatment intervention result in a significantly lower NPR level compared to the Sham Control at the post-treatment measure (OA3, our primary endpoint) after controlling for the baseline value. A 2 point reduction in NPR score will be considered a clinically-meaningful important difference.
  - We will use separate analyses to test whether the manipulation or mobilization treatment intervention result in a significantly lower RMDQ level compared to the Sham Control at the post-treatment measure (OA3, our primary endpoint) after controlling for the baseline value. A 3 point reduction in RMDQ score will be considered a clinically-meaningful important difference.
- Secondary Hypotheses
  - We will use separate analyses to test whether the manipulation or mobilization treatment intervention result in a significantly lower PROMIS-based outcome measures compared to the Sham Control at the post-treatment measure (OA3, our primary endpoint) after controlling for the baseline value.
- Exploratory analysis
  - To examine the immediate and longitudinal effects of the manipulation and mobilization treatment interventions, we will examine whether the treatment groups display significantly lower levels in NPR and/or RMDQ than the Sham Control at the other endpoints (i.e., OA2 and OA4), after controlling for the baseline value as a covariate.
  - We will use separate analyses to test whether the manipulation treatment intervention results in a significantly different NPR or RMDQ level compared to the mobilization treatment intervention at the post-treatment measure (OA3, our primary endpoint) as well as the other endpoints after controlling for the baseline value.

For all analyses two-tailed comparisons will be made with a pre-set significance level of 0.05. For all analyses, if there is a significant main effect, then we will perform Fisher's Least Significant Difference (LSD) to examine which group significantly differs from which without any adjustment. .

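### The co-primary comparisons with sham are one-tailed in section 9.1 and two-tailed at 0.05 in section 9.5, so the plan holds two decision thresholds for its primary result

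*Supplement*

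**What the plan says.** - **Section 9.1, RCT Component, Primary Hypotheses.** Both manual therapies are expected to give lower NPR and lower RMDQ than sham at OA3, adjusted for baseline. Each of the two hypotheses ends with the same rule: "Because we have a directional hypothesis, we will use a one-tailed test". No alpha is attached to it.
- **Section 9.5, RCT Component.** The same comparisons are listed as separate analyses, for example "whether the manipulation or mobilization treatment intervention result in a significantly lower NPR level compared to the Sham Control". The subsection closes with "For all analyses two-tailed comparisons will be made with a pre-set significance level of 0.05". The next sentence adds that, after a significant main effect, Fisher's LSD is used "to examine which group significantly differs from which without any adjustment".
- **Section 9.2, simulation assumptions** (listed for the Mechanistic Component). "The Type I error rate (the alpha level) was set at 0.05", with no sidedness, and "Holm's method was used to adjust the alpha level".
- **Section 9.2, Sample Size for RCT Component.** "Our simulation studies indicate that 54 subjects/treatment arm is sufficient to achieve power of 0.80", at d=0.5 with 10% attrition and alpha adjustments that are not specified. Sidedness is again absent.

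All of this is current text. Nothing says which section prevails, and nothing sets the one-tailed test at 0.025, which would have made the two rules agree for a favourable result.

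**The concern.** The two rules apply to the same tests and have different critical values. For a co-primary outcome the threshold separates a positive finding from a negative one, so it should be fixed before treatment codes are released. As written, a result in favour of manual therapy that falls between the two thresholds could be reported either way, and each report could cite the plan. The power statement has the same gap, because a reader cannot tell which test the 0.80 belongs to.

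**Working it through.** **Inputs from section 9.2:** 54 per arm; 10% attrition, so 54 × 0.9 = 48.6 evaluable; d=0.5; SD 2.5 for NPR and 6 for RMDQ; alpha 0.05. The correlation between baseline and outcome is not given, so it is assumed here over the range 0 to 0.7.

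**Step 1. The plan's own 0.80.** In the normal approximation, power = Φ(d√(n/2) − z). With n=48.6, d√(n/2) = 0.5 × √24.3 = 2.465.
- One-sided 0.05: Φ(2.465 − 1.645) = 0.794 (noncentral t: 0.789).
- Two-sided 0.05: Φ(2.465 − 1.960) = 0.693 (noncentral t: 0.684).

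The one-sided figure matches 0.80, but only with no baseline gain and no alpha adjustment, although section 9.2 mentions both. With an assumed baseline correlation r, d is replaced by d/√(1 − r²):

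| Assumed r | One-sided | Two-sided |
|---|---|---|
| 0 | 0.794 | 0.693 |
| 0.3 | 0.826 | 0.734 |
| 0.5 | 0.885 | 0.812 |
| 0.7 | 0.965 | 0.932 |

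(Normal approximation. At r=0.5 the noncentral t gives 0.881 and 0.804.) Two-sided testing with r=0.5 also comes close to 0.80, so the stated power does not show which tail was used.

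**Step 2. The disputed band.** SE = SD × √(2/48.6): 0.507 for NPR and 1.217 for RMDQ. Critical t on about 95 df is 1.661 one-sided and 1.985 two-sided.
- NPR: 0.507 × 1.661 = 0.84 and 0.507 × 1.985 = 1.01 points.
- RMDQ: 1.217 × 1.661 = 2.0 and 1.217 × 1.985 = 2.4 points.

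The normal approximation gives 0.83 to 0.99 and 2.00 to 2.39. At r=0.5 the SE shrinks by √0.75, and the t-based bands become 0.73 to 0.87 and 1.75 to 2.09.

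**Step 3. Error rates if the contrasts are tested directly.** With no true effect, the chance of a significant result in favour of treatment is 5% per comparison under 9.1 and 0.05/2 = 2.5% under 9.5.

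**Step 4. Error rates if the main-effect gate applies first.** Simulation with 49 per arm, no covariate and a three-arm F test at 0.05 before the contrast:

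| True state | Quantity | One-tailed | Two-tailed | Share of band results passing the gate |
|---|---|---|---|---|
| All arms equal | false-favourable rate per comparison | 1.5% | 1.2% | about 10% |
| Both therapies at d=0.5 | power per comparison | 0.67 | 0.63 | about 40% |
| One at d=0.5, one null | false-favourable rate, null arm | 4.6% | 2.4% | about 87% |

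The gate shrinks the effect of the contradiction in the first two cases and barely does so in the third.

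**The case against.** The strongest reply is that the contradiction has limited reach.

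- The Fisher's LSD sentence may put a non-directional three-arm test in front of every contrast. Where it applies, the doubling from 2.5% to 5% is much reduced in some settings (step 4). This stands. But the primary bullets in 9.5 speak of separate analyses, which can equally mean ungated tests, so the gate is one reading and not a settled rule.
- The figures without a covariate are the least favourable. The plan adjusts for baseline, and section 9.2 lets some of the 10% drop out only at the four-week measure, so 48.6 at OA3 is conservative. With all 54, the normal approximation gives 0.830 and 0.738. This also stands, and is why the results are given as a range.
- The whole band lies below the plan's clinically meaningful differences of 2 NPR and 3 RMDQ points, and the RCT is an exploratory Phase II component. True, but the plan still names co-primary outcomes, a primary endpoint, a significance level and a power for them, and those need one rule.
- The two-tailed sentence follows the exploratory bullets. Its wording is nevertheless not limited to them.

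A reader might also infer that a one-tailed rule would stop the trial from reporting that a therapy did worse than sham. The documents do not support that: the Preliminary Analysis part of 9.5 plans confidence intervals around effect sizes, and the therapy-against-therapy comparison is worded non-directionally.

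**Conclusion.** The contradiction is real, concerns both co-primary outcomes and is not resolved anywhere in the documents. The plan states two thresholds. Its consequences are conditional:

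- For directly tested contrasts, favourable results with two-sided p of 0.05 to 0.10 change verdict, and the false-favourable rate is 5% or 2.5% per comparison. Behind the main-effect gate, fewer results change.
- At 48.6 per arm without baseline gain, the band is about 0.84 to 1.01 NPR or 2.0 to 2.4 RMDQ points, and power is about 0.79 or 0.68. At an assumed r=0.5, power is about 0.88 or 0.81. None of these figures includes a multiplicity adjustment.

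Three stronger inferences do not follow. The documents do not show that the tail would be picked after seeing the data: investigators and statistician stay blinded to assignment until the end, although blinding does not supply the missing rule. The match of 0.794 to 0.80 does not show that one-tailed testing was intended, because other combinations fit too. Nor does this point require familywise control at an overall 0.05. Section 9.5 declines adjustment, and whether it should is a separate question.

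**What to change.** Before unblinding:

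1. Delete the two one-tailed sentences in section 9.1.
2. State in 9.1 and 9.5 that the co-primary comparisons with sham are two-sided at the plan's 0.05, reported with two-sided confidence intervals.
3. In section 9.2, state the sidedness and restate the RCT power on that basis, giving the baseline correlation and any alpha adjustment used.

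The cost is text edits and no additional patients. Relative to the one-tailed reading, nominal power at d=0.5 falls by about 11 points with no baseline gain (0.79 to 0.68) and by about 8 points at an assumed correlation of 0.5 (noncentral t: 0.881 to 0.804), and by less if the correlation is higher. Relative to section 9.5 as it stands, nothing is lost.

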## 9.2 Sample Size and Randomization

### **Sample Size Calculation for Mechanistic Component**

For each primary hypothesis, sample size to achieve the power of 0.80 was computed using Monte Carlo simulation studies. For all simulation studies, the following were assumed:

- The Type I error rate (the alpha level) was set at 0.05 and the Type II error rate (the beta level = 1 - power) at 0.20.
- A first-order autoregressive temporal structure was assumed with  $\rho$  of -0.50.
- Holm's method was used to adjust the alpha level.
- To produce a plausible attrition rate, 10% of the computer-generated participants dropped out at either 2-days or 4-week post treatment measure completely at random; these participants contributed no scores at subsequent measures. To make the sample-size calculation slightly conservative, missing observations remained missing.
- Linear mixed effects regression (LMER) was used to analyze the data.
- To ensure the acceptable precision, each simulation study was repeated 10,000 times.
- The baseline measure was included as a covariate to improve power and precision of the test.

